### Baseline measures and follow up

The primary outcome measure is change in HbA1c between the baseline measurement at the assessment visit and 12-month visit. Secondary outcome measures include change in systolic and diastolic blood pressure, weight, serum cholesterol and HDL, self-reported smoking status, dietary intake and physical activity (the Diabetes Self Care Activities Questionnaire) [22], medication adherence (The Medication Adherence Rating Scale) [23], and the scores in the Diabetes Treatment Satisfaction Questionnaire [24], and the Well-being Questionnaire (12 item) [25].

Beliefs about diabetes and its management are assessed using the Illness perceptions Questionnaire [26], Beliefs about Medicines Questionnaire [27], and a questionnaire developed for the study about the effectiveness of changes in eating and physical activity on the course of diabetes, and attitudes to blood glucose self-monitoring. Table 1 summarises the measures and their timing.

**Table 1 T1:** Study measures

**Measures**	**Baseline**	**3 months**	**6 months**	**9 months**	**12 months**
**Questionnaire measures:**					
Illness perceptions questionnaire [26]					
Well-being questionnaire 12-item [25]					
Beliefs about medicines questionnaire					
Medication Adherence Report scale					
Beliefs about physical activity and eating +					
Beliefs about blood glucose monitoring +					
Beliefs about using a blood glucose monitor+					
Occupation and social class					
**Physiological measures**					
HbA1c					
Blood pressure					
Weight, height					
Total and HDL cholesterol					
**Costs**					
Use of medical services					
Costs of medication					
Costs of delivering intervention					

Blood glucose monitoring resources are measured by counting recorded entries in diaries. Medication use, episodes of hospitalisation and their duration will be noted and non-hospital health care resource use will be recorded by a questionnaire administered to all patients at each visit.

### Trial procedures

#### Assessment

Participant eligibility for the study and willingness to be randomised to a group in which they might be required to test their own blood glucose six times a week or more is confirmed at the assessment visit. Following consent, beliefs about diabetes, the role of eating, physical activity and medication are discussed with all participants. A goal setting approach to lifestyle change is introduced and continued in subsequent visits. Baseline blood tests and clinical measurements are taken and questionnaires completed at this visit.

Following the assessment visit and confirmation of eligibility on the basis of HbA1c measurement, patients are randomised to one of three groups: control group, self-testing and self-monitoring.

#### Post-randomisation

At a visit two weeks after the assessment visit participants receive training and education appropriate to their allocated study group. The control group receives 3-monthly HbA1c measurements and identifies behavioural goals to improve glycaemic control. The self-testing group, in addition, is asked to use a blood glucose meter to record three fasting, pre-meal or 2-hour post meal readings on two days during the week. Treatment targets of fasting and pre-meal levels of 4–6 mmol/l and post meal levels of 6 to 8 mmol/l and advice about using these readings to identify high (>15 mmol/l) and low (<4 mmol/l) blood glucose readings are given. The self-monitoring group, in addition, is provided with training and support to encourage interpretation of readings and application to goals for lifestyle change based on the CSM in order to reach treatment targets.

#### Follow up visits

Subsequent follow up includes a telephone call 2 weeks after randomisation (after the post-randomisation visit rather than randomisation), and further visits at 4, 13, 26 and 39 weeks. The follow up visits differ according to the allocated group. Those allocated to the control group have a HbA1c measure two weeks before their scheduled visit in order for their glycaemic control to be discussed. The two groups using a meter are managed on the results of their blood glucose self-monitoring. The GP is notified of all HbA1c results and asked to consider changes in medication in line with the National Institute for Clinical Excellence diabetes guidelines. The GP is also notified if blood glucose readings are consistently above 15 mmol/l.

#### Study measures (see Table 1 and Figure 1)

Baseline self-report measures and measures of belief are completed at the assessment visit. Baseline biochemical measures and clinical measurements are also made. Repeated measurements are made at the 52-week follow up visit. Data on adverse reactions or complications are collected at each study visit along with information about use of medication and health services.

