**Figure 1 F1:**
[figure not shown]
Consort diagram showing planned study numbers.

The study design is shown in Figure 1. Participants are randomised to three groups consisting of

(i) a control group receiving standardised usual care and three monthly measurement of HbA1c,

(ii) a self-testing group who, in addition to the above, are carrying out blood glucose self testing with the results interpreted by the study nurse,

(iii) a self monitoring group who, in addition to both of the above, are given support in interpreting and applying the results of blood testing to enhance motivation and maintain adherence to diet physical activity and medication regimens.

Following randomisation, patients receive the allocated education and training appropriate for their group, with follow up to maintain the interventions at four, 13, 26, and 39 weeks with a final assessment at 52 weeks.

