## Discussion

This study will make an important contribution to the evidence-base for the use of blood glucose self-monitoring in non-insulin using patients with type 2 diabetes. It will provide a robust estimate of overall effect of use of the meters for self-testing alone and with a more intensive programme to support people in using their test results actively in self management of health related behaviours.

This trial will address two main problems associated with previous trials. Firstly, the study is adequately powered to identify a reduction in HbA1c of 0.5%, which is associated with clinically important reductions in diabetic complications. Secondly, study participants allocated to the most intensive group are explicitly supported in interpretation of their study results in relation to lifestyle changes. This is the first study in this field to use standardised delivery of these interventions together with the other measures supporting fidelity to protocol.

A further strength of the trial design is the inclusion of measures that explore the extent to which the interventions being used influences beliefs and behaviour. It will be possible to test whether the interventions, especially that based on the CSM, are successful in altering beliefs about diabetes, and whether the interventions were delivered with fidelity to their theoretical basis. It will also be possible to test whether differences in behaviour and HbA1c between experimental groups are due to the interventions bringing about changes in beliefs, as proposed by the CSM. Depending on the pattern of findings from the mediation analysis, it will be possible to conclude there is no mediation (none of the causal effect of intervention on behaviour is transmitted by beliefs about diabetes), total mediation (all of the effect is transmitted by beliefs) or partial mediation (part of the effect is transmitted by beliefs and part is direct). This will provide information about the extent to which the CSM can usefully inform intervention content to change beliefs and behaviours.

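### The Discussion promises causal verdicts of no, total or partial mediation through beliefs that the design cannot support

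*Protocol article*

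**What the plan says.** On timing, the section on study measures states "Baseline self-report measures and measures of belief are completed at the assessment visit", and then "Repeated measurements are made at the 52-week follow up visit". What it lists for every visit does not include beliefs: "Data on adverse reactions or complications are collected at each study visit along with information about use of medication and health services". The full schedule is in a table (Baseline measures and follow up): "Table 1 summarises the measures and their timing". That table has columns for baseline and 3, 6, 9 and 12 months and rows for the belief questionnaires, but its cell entries are not legible in the text available.

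On the outcome: "The primary outcome measure is change in HbA1c between the baseline measurement at the assessment visit and 12-month visit". Dietary intake, physical activity and medication adherence are measured by questionnaire.

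On the analysis, the Abstract and Statistical aspects introduce mediation as exploratory. Mean beliefs are first compared between groups, and a formal mediation analysis, described by citation, follows. The Discussion goes further. It says the trial can test "whether differences in behaviour and HbA1c between experimental groups are due to the interventions bringing about changes in beliefs". It adds that, depending on the results, one may conclude that beliefs transmit none of the causal effect on behaviour, or that there is "total mediation (all of the effect is transmitted by beliefs) or partial mediation". No assumption about temporal order or belief-outcome confounding is stated.

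**The concern.** Randomisation protects two comparisons: the effect of arm on beliefs and the effect of arm on outcome. It does not protect the path from belief to outcome, on which any mediation verdict turns.

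Two features of this trial make that path hard to read causally. First, feedback on glycaemia is part of every arm. Controls have HbA1c measured before scheduled visits so that it can be discussed, and the meter groups are managed on their own readings (Follow up visits). Achieved control can therefore shape beliefs about how controllable diabetes is, which is the example of a belief given in Statistical aspects. Second, on the running text the belief scores and the self-reported behaviours they should explain are repeated at the same visit, so their order in time is not observed.

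Secondary objective (iii) and a strength claimed in the Discussion rest on this analysis. It is meant to show how far the Common Sense Model can inform intervention content. A belief that partly reacts to good or bad results could be credited as a route by which the intervention works.

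**Working it through.** **1. The plan's own figure.** Inputs from Statistical aspects: 135 per group after attrition, SD 1.2, difference 0.5%, two-sided 5%. The standard error of the difference is 1.2 × √(2/135) = 0.146, and 0.5/0.146 = 3.42. Power = Φ(3.42 − 1.96) = 92.8%, which reproduces the stated 93%. This figure concerns the HbA1c difference between two groups. No power is stated for either mediation path.

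**2. Beliefs react to the outcome, with no mediation.** Let T be arm (0/1), Y the outcome with within-arm SD 1, δ the effect of arm, M the belief score and ρ the within-arm correlation. Signs are chosen so that both move the same way.
- Truth: Y = δT + e and M = ρY + √(1 − ρ²)·e′. There is no path from M to Y.
- Arm to belief: a = ρδ.
- Belief to outcome given arm: b = Cov(Y, M | T)/Var(M | T) = ρ/(ρ² + 1 − ρ²) = ρ.
- Apparent indirect effect: ab = ρ²δ. The total effect is δ, so the share that appears mediated is ρ².

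The documents give no ρ, so these values are assumptions:

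| Assumed ρ | Share that appears mediated |
|---|---|
| 0.3 | 0.3² = 9% |
| 0.4 | 0.4² = 16% |
| 0.5 | 0.5² = 25% |

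The share does not depend on δ or on sample size. A simulation of 3,000 trials with 135 per arm, δ = 0.5/1.2 = 0.417 and ρ = 0.4 gave 15.8%, in agreement.

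**3. Arm affects both, and a shared cause links them, with no mediation.** Let M and Y each equal δT plus a common cause contributing within-arm correlation c. Then a = δ and b = c, and the apparent share is cδ/δ = c. At an assumed c = 0.4 it is 40%. Measuring beliefs earlier does not remove this if the shared cause persists.

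**4. What verdict would be returned.** The decision rule is not in the article. For illustration I assume that mediation is declared when the total effect and both paths are significant, and is called total if the direct effect is then non-significant. Each row is 3,000 simulated trials, 135 per arm, total effect 0.4 SD.

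| Truth | Total | Partial | Either |
|---|---|---|---|
| Beliefs react, ρ = 0.4 | 4.0% | 22.3% | 26% |
| Shared cause, c = 0.4 | 34.1% | 49.6% | 84% |
| Full mediation, a = 1.0, b = 0.4 | 87.3% | 3.1% | 90% |

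The rows are not matched on the effect of arm on belief, so their rates should not be ranked. They show that three causal structures, two of them without mediation, can each return a total or partial verdict from the same kind of data.

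**The case against.** The strongest objection concerns timing. A reader might infer that beliefs are re-measured only at 52 weeks. The article never says so. Table 1 has 3-, 6- and 9-month columns whose entries cannot be read, and the sentence about repeating measurements is not exhaustive. It follows a sentence on biochemical measures, yet the design includes "a control group receiving standardised usual care and three monthly measurement of HbA1c". An interim belief measure may already exist. This stands, and the point does not depend on its absence.

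A reader might also infer that a merely reactive belief would be reported as the mechanism of effect, or that a verdict of none or total amounts to reading a non-significant path as zero. Neither is supported. The correlations are assumed, a spurious share of 9% to 25% does not by itself produce a wrong verdict, and the decision rule lies in a cited source that is not shown. Adjustment sets and interval methods may properly sit in a fuller plan, so their absence here is no fault.

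Two further objections have force. The none, total or partial verdicts are worded for behaviour, and HbA1c appears in a separate sentence; the algebra holds for either outcome, but the size of ρ may differ. Nothing says participants know their 52-week HbA1c when they complete the questionnaires, so any reaction would be to earlier readings, which could weaken the link.

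The analysis is also exploratory as introduced. That limits the consequence, but it sharpens the mismatch with the Discussion, which claims firm causal conclusions.

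**Conclusion.** The point holds as an overclaim in the Discussion. The design cannot deliver verdicts of no, total or partial mediation of a causal effect, nor attribute outcome differences to changed beliefs. Beliefs are not randomised, and glycaemic feedback in all arms gives a plausible reverse route. The same-visit measurement described in the running text adds to the difficulty, subject to what Table 1 shows.

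The size is illustrative. With no true mediation, about 9% to 25% of the effect would appear mediated at assumed belief-outcome correlations of 0.3 to 0.5.

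It would go too far to say that an interim belief measure would settle the matter. Beliefs at 26 weeks would still follow months of readings and feedback, and shared causes of belief and behaviour would remain. The primary HbA1c comparison, its power and the randomised comparison of mean beliefs between arms are untouched. The change is worth making because it alters what the trial may conclude on secondary objective (iii).

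**What to change.** - Report the indirect and direct effects with confidence intervals (bootstrap, for example), adjusted for baseline belief, baseline outcome and the minimisation factors. The article names duration of diabetes, HbA1c and prior medication among these.
- Add a sensitivity analysis showing how strong belief-outcome confounding would have to be to remove the indirect effect.
- If Table 1 includes interim belief measures, use these as the mediator of 52-week behaviour and HbA1c. Keep the sensitivity analysis, since earlier measurement does not deal with confounding.
- In the Discussion, replace the none, total or partial verdicts with association consistent with mediation, and soften the claim that differences are due to changed beliefs. State the temporal-order and no-confounding assumptions there.

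The cost is a little more analysis and a more modest secondary claim. No new data are required.

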#### Quality assurance and fidelity of interventions

Patients are supplied with a blood glucose meter calibrated to provide plasma equivalent results. Meters are checked at the beginning of the study and at 26 weeks by study nurses with a test aliquot.

A script outlining the topics to be covered, and explanation of the theoretical basis of the intervention are used to support the nurses in their adherence to study protocol. Study nurses attended a six day phased course in psychological theory, behaviour change techniques and skills training in the intervention. Additional measures to ensure fidelity include self-review of taped interventions by the study nurses and external review by a researcher using a checklist to ensure delivery of the intervention according to protocol. Prompts built into the patient diaries help participants adhere to their allocated group intervention.

#### Statistical aspects

In the absence of data relating to change in HbA1c we have calculated sample size conservatively based on the absolute level of HbA1c at follow up. We set out to detect a difference in HbA1c of 0.5% between any two groups. At the outset we estimated the SD of HbA1c as 1.5, based on data from the UKPDS. In practice, the SD of baseline HbA1c among the 245 patients recruited in Oxford was 0.9, but we assumed that the SD among additional patients recruited elsewhere could be as high as 1.5. With 205 further patients, the overall SD would be 1.2, and there would be 150 patients in each group (135 allowing for 10% attrition). These numbers would give 93% power to detect a difference of 0.5% in HbA1c between any two trial groups (2-tailed alpha = 0.05). Figure 1 gives estimates of likely numbers in each group and attrition.

We propose to conduct a single analysis of main trial endpoints at the end of the study. The proposed intention to treat analysis will compare mean levels of HbA1c at follow up between the three study groups, with baseline HbA1c as a covariate, using analysis of covariance. Post-hoc t-tests between groups will be conducted in the event of a statistically significant result. Subsequent analysis will include comparing the two intervention groups against the control group.

We will estimate the intervention effect in sub-groups defined by duration of diabetes (above or below median duration), current management (oral hypoglycaemic dugs or dietary management only), health status at baseline (above or below median EQ-5D score) and co-morbidity (presence or absence of diabetes related complications). We will also explore the extent to which the measures of beliefs included in the study can explain changes in behaviour; firstly by comparing mean levels of beliefs e.g. about controllability of diabetes between experimental groups and secondly by a more formal mediation analysis [28]. Within group analyses will be used to determine fidelity to protocol and conformity to the theoretical model, between group analyses will be used to assess impact of the intervention on key variables proposed by the theoretical model. Additional exploratory analysis will include changes in behaviour in relation to perceived threat and changes in perceived thereat from diabetes.

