### Randomisation

Participants are randomly allocated to one of the three groups using a partial minimisation procedure to adjust the randomisation probabilities between groups to balance important covariates including duration of diabetes, HbA1c, and prior medication using a computer programme (Minim, ).

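### The primary ANCOVA names only one of the three minimisation factors, so its standard errors may be slightly too large

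*Protocol article*

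**What the plan says.** Under Randomisation, the article allocates to three arms "using a partial minimisation procedure to adjust the randomisation probabilities between groups", in order to "balance important covariates including duration of diabetes, HbA1c, and prior medication". The list is introduced as examples, so there may be further factors.

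Under Statistical aspects, the proposed intention-to-treat analysis compares mean follow-up HbA1c across the three arms "with baseline HbA1c as a covariate, using analysis of covariance". Post-hoc t-tests between arms follow if the overall result is significant. Duration and current management reappear in that section only as subgroup variables. Neither is added to the primary model, and no re-randomisation test is mentioned that would respect the allocation in another way.

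**The concern.** Minimisation makes the arms more alike on its factors than simple randomisation would. If those factors predict the outcome, the true sampling variance of the difference between arms is smaller than under simple randomisation. A model that omits them keeps their contribution in the residual variance and so reports the larger standard error that fits simple randomisation. Intervals are then too wide, p-values too large, and the actual type I error lies below its nominal level.

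What is at stake is a modest loss of reported precision on the primary outcome. Baseline HbA1c is both minimised and adjusted for, so the concern is confined to duration, prior medication and any unnamed factor.

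**Working it through.** **Inputs from Statistical aspects.** The target is stated as "We set out to detect a difference in HbA1c of 0.5% between any two groups". For the spread, "With 205 further patients, the overall SD would be 1.2". For numbers, "there would be 150 patients in each group (135 allowing for 10% attrition"), which is 3 × 135 = 405 completers. The result is given as "These numbers would give 93% power to detect a difference of 0.5% in HbA1c between any two trial groups (2-tailed alpha = 0.05").

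**Input not in the article.** Let R² be the share of residual variance, after baseline HbA1c, that duration and prior medication explain. I assume 2% to 10% as the working range and show 0%, 20% and 30% as well.

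**Step 1: reproduce the plan's figure.**
- Pooled SD = √[(245 × 0.9² + 205 × 1.5²) / 450] = √(659.7 / 450) = 1.21, in agreement with 1.2.
- SE of a pairwise difference = 1.2 × √(2/135) = 0.146.
- Power = Φ(0.5/0.146 − 1.96) = 92.8% (92.7% with the noncentral t).

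The stated 93% reproduces.

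**Step 2: effect of leaving out balanced factors.** With near-complete balance, true variance = (1 − R²) × model variance. Hence:
- model SE / true SE = 1/√(1 − R²)
- actual two-sided error of a nominal 5% test = 2 × [1 − Φ(1.96/√(1 − R²))]

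| R² | SE ratio | Actual error |
|---|---|---|
| 0% | 1.000 | 5.0% |
| 2% | 1.010 | 4.8% |
| 5% | 1.026 | 4.4% |
| 10% | 1.054 | 3.9% |
| 20% | 1.118 | 2.8% |
| 30% | 1.195 | 1.9% |

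**Step 3: effect on power.** Using the plan's SD of 1.2 as the residual SD before these factors enter:
- factors omitted: power = Φ[(0.5/0.146 − 1.96)/√(1 − R²)]
- factors included: SE = 0.146 × √(1 − R²), and power = Φ(0.5/SE − 1.96)

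| R² | Power, omitted | SE, included | Power, included |
|---|---|---|---|
| 2% | 93.0% | 0.145 | 93.3% |
| 5% | 93.3% | 0.142 | 94.0% |
| 10% | 93.9% | 0.139 | 95.0% |
| 20% | 94.9% | 0.131 | 96.9% |

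Within the working range, adjustment is worth between 0.3 points (93.3 − 93.0) and about 1 point (95.0 − 93.9) of power over the same design analysed without the factors.

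**Step 4: simulation.** Three-arm minimisation was simulated on three binary factors with 405 patients. Each patient went to the best-balancing arm with probability 0.8 and otherwise to a random arm (an assumption, as the article gives no probability). There were 1,500 runs per setting.

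| R² | SE ratio, HbA1c only | Error, HbA1c only | SE ratio, all factors | Error, all factors |
|---|---|---|---|---|
| 0% | 0.98 | 5.4% | 0.98 | 5.4% |
| 5% | 1.02 | 5.0% | 1.00 | 5.2% |
| 10% | 1.04 | 4.2% | 0.99 | 5.1% |
| 20% | 1.10 | 2.5% | 0.98 | 4.7% |
| 30% | 1.23 | 1.5% | 1.03 | 3.7% |

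Monte Carlo error is about 0.6 points on the error rate (√(0.05 × 0.95/1500)) and about 2% on the SE ratio (1/√(2 × 1500)). The direction agrees with Step 2. At R² of 5% and 10% the gap from the formula is within simulation noise, and at 5% the simulation shows no detectable distortion of the test.

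**The case against.** The strongest reply has three parts.

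First, the effect is conditional. At R² = 0 nothing happens, and the article gives no prognostic strength for duration or prior medication. It does call the minimisation factors important, but that word covers HbA1c as well and does not speak to what the others add once baseline HbA1c is in the model. This stands, so the size can only be given as a range under an assumption.

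Second, the formula assumes near-complete balance. The article describes a partial procedure that keeps a chance element, and duration may be minimised in categories, which leaves variation within categories unbalanced. This also stands: the Step 2 figures are upper bounds for a given R².

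Third, this is a condensed article, and naming one covariate does not formally exclude others. This has some force. But the article does state its model and its covariate, and as stated they do not match its own allocation. The point is about that mismatch, not about missing detail.

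Two stronger readings are tempting and should be set aside.
- **Centre.** A reader might infer that centre must be in the model because the two centres are expected to differ in HbA1c. The article gives only a cautious planning assumption about spread (0.9 observed, possibly up to 1.5) and says nothing of different means. A centre term adjusts for means, not for unequal variances. Nor is centre named as a minimisation factor.
- **Lost precision.** A reader might infer that the gain from minimisation is thrown away. It is not. The estimated difference keeps the benefit of balance, and only the reported standard error and p-value fail to credit it.

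**Conclusion.** The mismatch is real and minor in effect. Three factors are named for allocation and one for the primary model. If duration and prior medication explain 2% to 10% of residual variance, the standard error is overstated by at most about 1% to 5%, and a nominal 5% test runs at between 4.8% and 3.9%. Adjusted pairwise power would be about 93% to 95%. Those figures rest on the assumed R² and on near-complete balance.

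The documents do not support reading this as bias or as type I error inflation: the direction is conservative. Nor does it undermine the 93% power, which rests on the unadjusted SD and reproduces.

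A reader might also suppose that the post-hoc t-tests drop baseline HbA1c, which would make the loss larger. The article does not say whether those tests are adjusted, so that cannot be asserted. It is a reason to settle the source of the contrasts.

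**What to change.** State the primary model as an ANCOVA of follow-up HbA1c on arm, baseline HbA1c, duration of diabetes, prior medication and any other minimisation factor actually used. Take all pairwise arm contrasts from this model in place of separate post-hoc t-tests. Include centre only if it was a minimisation factor.

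The cost is a sentence in the plan and a few degrees of freedom out of about 400. The named factors have to be known before a patient can be allocated, so no new data are needed. Fixing the covariates before the analysis also removes any data-driven choice among them.

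### The pairwise HbA1c comparisons are named as post-hoc t-tests, without carrying forward the baseline adjustment of the three-group ANCOVA or saying whether level or change is tested

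*Protocol article*

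**What the plan says.** All references are to the protocol article.

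- **Three-group test (Statistical aspects).** The intention-to-treat analysis compares mean follow-up HbA1c across the three groups by ANCOVA, with baseline HbA1c as covariate.
- **Pairwise step (same section).** The next sentence reads: "Post-hoc t-tests between groups will be conducted in the event of a statistically significant result". Nothing says whether these tests are adjusted, or on which scale. The sentence after it announces comparisons of the two intervention groups with control and names no method.
- **Outcome (Baseline measures and follow up).** "The primary outcome measure is change in HbA1c between the baseline measurement at the assessment visit and 12-month visit". The ANCOVA is described on follow-up level instead.
- **Primary objective.** Whether HbA1c is lower in each of the two intervention groups than in control. This is a pairwise question.
- **Randomisation.** HbA1c is one of the covariates balanced by a partial minimisation procedure.
- **Sample size (Statistical aspects).** "We set out to detect a difference in HbA1c of 0.5% between any two groups", and "we have calculated sample size conservatively based on the absolute level of HbA1c at follow up".

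**The concern.** A three-group F-test shows only that the groups differ somewhere. The primary objective is answered by the pairwise differences, and the only pairwise method the article names is the t-test. In its ordinary sense, a t-test between groups compares two means using the data of those two groups. It uses neither the baseline covariate nor the residual variance pooled over all three groups.

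On that reading, the estimates and intervals that readers will use come from a less precise method than the test that opens the door to them. Because the arms are balanced on HbA1c by design, an analysis that ignores HbA1c also tends to overstate the standard error. Using two different models in sequence makes it more likely that a significant overall result is followed by pairwise results that do not agree with it.

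**Working it through.** **Inputs from the Statistical aspects section:** difference 0.5; SD 1.2 (0.9 in 245 patients, up to 1.5 assumed in 205 more); 135 analysed per group; two-sided alpha 0.05; stated power 93%.

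**Assumed, not in the article:** the correlation r between baseline and 12-month HbA1c, shown at 0.3, 0.5 and 0.7; equal SDs at both times; a common linear slope on baseline.

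**1. Reproduce the stated power.**
- Pooled SD = sqrt((245 × 0.81 + 205 × 2.25)/450) = 1.21, in line with the stated 1.2.
- SE of an unadjusted difference = 1.2 × sqrt(2/135) = 0.146.
- Power for 0.5 = 92.8% (normal approximation) or 92.7% (noncentral t).

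The 93% is therefore the power of a two-sample comparison of follow-up level with no baseline adjustment.

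**2. Compare three versions of the pairwise step.** In units of SD², the variance per patient is 1 for unadjusted follow-up, 2(1 − r) for change and 1 − r² for ANCOVA. Relative to ANCOVA:
- unadjusted follow-up: 1/(1 − r²)
- change: 2(1 − r)/(1 − r²) = 2/(1 + r)

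| | r = 0.3 | r = 0.5 | r = 0.7 |
|---|---|---|---|
| Variance ratio, unadjusted follow-up | 1.10 | 1.33 | 1.96 |
| Variance ratio, change | 1.54 | 1.33 | 1.18 |
| SE, unadjusted follow-up | 0.146 | 0.146 | 0.146 |
| SE, change | 0.173 | 0.146 | 0.113 |
| SE, ANCOVA | 0.139 | 0.126 | 0.104 |
| Power, unadjusted follow-up | 92.8% | 92.8% | 92.8% |
| Power, change | 82.5% | 92.8% | 99.3% |
| Power, ANCOVA | 94.8% | 97.7% | 99.8% |

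For unadjusted follow-up, the square roots of the variance ratios give intervals about 5%, 15% and 40% wider than ANCOVA. In information, this equals using 135 × (1 − r²) = 123, 101 or 69 of the 135 patients per group.

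**3. Larger SD.** At the SD of 1.5 that the sponsor assumed at the outset, unadjusted power is 78.2%. ANCOVA gives 81.9%, 88.5% and 97.0% at the three values of r.

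**4. Effect of minimisation.** If baseline HbA1c were perfectly balanced, the true SE of the difference in follow-up means would be the ANCOVA one, while the t-test would still report the unadjusted one. The true size of a nominal 5% test would then be 2 × (1 − Φ(1.96/sqrt(1 − r²))), which is 2.4% at r = 0.5 and 0.6% at r = 0.7. These are limiting values.

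**The case against.** The strongest reply is that the article nowhere calls the t-tests unadjusted. After an ANCOVA, a t-test can be a test of adjusted means, which is the remedy proposed here, and a condensed article may leave that detail to the full protocol. A reader might infer that the plan has fixed plain two-sample tests. The wording does not establish that. Nor does it show that the t-tests alone answer the primary question, because the comparisons with control are listed separately without a method. What remains is that the article names a method for this step, its usual meaning does not match the model before it, and a reader cannot tell which is intended.

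A reader might also infer that the trial loses much of its precision or its planned power. The documents do not support that:
- An unadjusted follow-up comparison has the power the sponsor planned for.
- At SD 1.2, adjustment adds about 2 to 7 points of power.
- The loss depends on an r that is not given, and it is small for follow-up level at r = 0.3.
- The defined outcome is change. A t-test on change does use baseline and comes close to ANCOVA at r = 0.7.

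Last, the error rates of 2.4% and 0.6% should not be taken as the trial's real ones. They need perfect balance, whereas the minimisation is partial and covers several covariates. Only the direction stands: the tests would be conservative, so false positives are not the worry. Adjusted contrasts can also disagree with an overall F-test; using one model makes this less likely but does not rule it out.

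**Conclusion.** The point holds as a free improvement. The pairwise step is not specified as baseline-adjusted, its scale is left open, and the comparison with control has no method. Read literally, it gives up precision that the sponsor's own ANCOVA would deliver.

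For r between 0.3 and 0.7, the variance is 1.10 to 1.96 times that of ANCOVA if follow-up level is tested, and 1.54 down to 1.18 times if change is tested. ANCOVA is the more precise choice throughout this range, so the recommendation does not depend on knowing r; only the size of the gain does.

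The stated 93% power stands for an unadjusted comparison of follow-up level. It would not carry over to a t-test on change if r were below 0.5 (82.5% at r = 0.3), which is a further reason to settle the scale. The figures rest on SD 1.2, 135 per group, equal SDs at both times and a common slope.

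**What to change.** In the Statistical aspects section, replace the post-hoc t-tests with pairwise contrasts of adjusted means from the same ANCOVA of 12-month HbA1c on group and baseline HbA1c, using its pooled residual variance. Report each contrast as a difference with 95% CI and p-value. State that the comparisons of each intervention group with control come from this model too. With baseline as a covariate, the group contrasts are the same whether the response is follow-up level or change, so this also settles the scale.

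The cost is wording only. Baseline HbA1c is measured at the assessment visit and is needed to confirm eligibility before randomisation, so no new data are required. The sample size need not change.
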